### 5.2.1 RADIOLOGICAL STAGING

The ability to reliably assess the degree of tumour regression on MRI (mrTRG) is fundamental to the success of the trial. To ensure consistency, a nominated study GI radiologist will be asked to participate in a CME-accredited trial-specific MRI reporting workshop/webinar. A site will not be able to open until the allocated radiologist(s) has achieved mrTRG competency (mrTRG kappa  $\geq 0.7$ ). The consultant radiologist can book a place on the MRI reporting workshop/webinar by contacting the TRIGGER Trial Office:

[name], Trial Manager, Academic Department of Radiology,

Royal Marsden Hospital, [name]

Email: [[contact]](mailto:[contact]) [contact] [contact]

## 5.3 REQUIRED SITE TRAINING

Prior to a site opening to recruitment, each site will be required to have at a minimum a site PI, one research nurse or trial coordinator and the nominated GI radiologist to participate in TRIGGER trial training. This training may be incorporated at a site initiation visit or participation in a teleconference. It is the responsibility of those who attend the training to disseminate the training to other site personnel.

## 5.4 SITE ACTIVATION

Following receipt of the documents listed in section 5.2 above and all required training is performed, written confirmation of site activation will be sent to the PI and all relevant site personnel. All trial-related materials will be provided to the site once they are activated and the site will be assigned a unique trial site code for use on trial-related documentation e.g. CRFs.

Following activation to TRIGGER:

- The site should conduct the trial in compliance with the protocol as agreed by the Sponsor, the MHRA and the REC.

- The PI or delegate should document and explain any deviation from the agreed protocol by completing the **PROTOCOL DEVIATION Form**, and communicate this with the trial team at the Royal Marsden.

## 5.5 THE DELEGATION LOG

All staff taking part in the trial are required to specify their trial responsibilities in the delegation log. These staff will then be authorised by signature to work on the trial by the PI. The log is important because it allows the PI to retain oversight of the staff working on the trial. The delegation logs may also be used to correctly acknowledge individuals in presentations and publications.

All investigators should sign the delegation log and the site PI must co-sign the delegation log to delegate duties and acknowledge overall responsibility for the trial site. Only an appropriately qualified and trained investigator who has a thorough understanding of the trial may take consent.

## 6. PATIENT ELIGIBILITY CRITERIA

The TRIGGER trial will recruit patients undergoing pre-operative treatment for locally advanced rectal cancer. Participants will be considered eligible if they fulfil all the inclusion criteria and none of the exclusion criteria as defined below. The Eligibility Checklist included on the **TRIAL REGISTRATION Form** should be completed to confirm eligibility and signed by the investigator.

### 6.1 INCLUSION CRITERIA

Patients must fulfil **ALL** of the following inclusion criteria to be considered eligible for the TRIGGER Trial:

- 1) Have a biopsy-confirmed adenocarcinoma 0-15cm from the anal verge (on MRI or rigid sigmoidoscopy).
- 2) Have locally Advanced Rectal Carcinoma diagnosed by MRI (mrCRM unsafe or  $\geq$ mrT3c [ $>5$ mm beyond muscularis propria] or mrEMVI positive disease)
- 3) Be deemed to require chemoradiotherapy.
- 4) Scheduled to receive 45Gy - 55Gy long course radiotherapy.
- 5) Have provided written informed consent to participate in the study.
- 6) Be aged 18 years or over.

The inclusion criteria above should be re-checked at the Randomisation visit.

### 6.2 EXCLUSION CRITERIA

Patients will **not** be eligible for the TRIGGER Trial, if they fulfil any of the following:

- 1) Have metastatic disease (including resectable liver metastases).
- 2) Are contraindicated for MRI e.g. non-MR compatible hip prosthesis, cardiac pacemaker.
- 3) Are scheduled to receive less than 45Gy or more than 55Gy long course radiotherapy.
- 4) Are contraindicated for chemoradiotherapy (CRT)
- 5) Hypersensitivity or contraindication to the drug(s) associated with the planned choice of systemic chemotherapy (CAPOX, FOLFOX or single agent 5-FU or capecitabine) as stated in the SmPC for each of the drugs.
- 6) Are receiving or planned to receive treatment outside of that stipulated by the protocol, such as an alternative cytotoxic or investigational drug.
- 7) Are pregnant, breastfeeding or unable / unwilling to comply with pregnancy prevention guidelines\*.
- 8) Any other malignant disease within the preceding 5 years with the exception of non-melanomatous skin cancer, carcinoma in situ and early stage disease with <5% recurrence risk.

\* Females of childbearing potential and males must be willing to use a highly effective method of contraception. Contraceptive methods that can achieve a failure rate of less than 1% per year when used consistently and correctly are considered as highly effective birth control methods. Contraceptive measures should be compliant with those described in the Summary of Product Characteristic for each of the IMPs used in this trial.

**The exclusion criteria above should be re-checked at the Randomisation visit.**

## **7. REGISTRATION AND RANDOMISATION**

### **7.1 INFORMED CONSENT**

The study will be conducted in accordance with the clinical trials regulations, the principles of GCP and the Declaration of Helsinki. Informed consent will be taken by the Principal Investigator or an appropriately qualified, trained and delegated clinician. The process for giving information to patients has a two-step staged approach to reduce the possibility of information overload and providing patients with plenty of time for consideration of participation in the main TRIGGER trial.

#### **7.1.1 PATIENT INFORMATION SHEET 1 – REGISTRATION**

This PIS contains general information about the main TRIGGER trial with consent for transfer of an archival block of tumour tissue to a central laboratory for further analysis, Quality of Life questionnaire completion,

the optional the collection of a blood sample for the assessment of proliferative, apoptotic and genomic markers, and consent to collect clinical outcome data regardless of if the patient is subsequently randomised into TRIGGER. This PIS is kept as minimal and as simple as possible whilst still providing sufficient information for the patient to give informed consent for registration. Suitable patients will be approached for entry into the registration period of TRIGGER at a routine outpatient clinic during the 4 weeks prior to commencing CRT. Once a patient is identified as potentially eligible, the rationale for this part of the study will be explained, the patient will be provided with Patient Information Sheet 1 and they will be given the opportunity to ask questions. The patient may then be consented for registration. When consent has been obtained and eligibility confirmed (using the Eligibility Checklist on the **TRIAL REGISTRATION Form**), baseline data should also be collected and recorded on the **TRIAL REGISTRATION Form**.

### **7.1.2 PATIENT INFORMATION SHEET 2 – RANDOMISATION**

This PIS contains full details of the TRIGGER Trial and will be given to suitable patients during the registration period of TRIGGER either at an outpatient clinic or chemoradiotherapy appointment. Written informed consent for the main trial period will be obtained at a routine visit during CRT or once CRT is complete but at least 1 week prior to the post-CRT MRI scan.

Patients wishing to receive information about the main TRIGGER trial before providing consent for registration may receive Patient Information Sheet 2 at their first appointment if they wish.

The original signed consent forms at both registration and randomisation should be stored in the site investigator file. Four copies of the consent form should be made: one copy for the trial patient, one stored in the hospital notes, one copy sent to the local pathology lab for archived tissue release and one sent to the TRIGGER Trial Office for central monitoring processes.

If new information becomes available which may be relevant to the patient's consent, forms will be revised and informed consent sought again. Following consent and randomisation a letter must be sent to the patient's General Practitioner (Template provided at site initiation).

### **7.1.3 SCREENING, REGISTRATION AND RANDOMISATION LOGS**

The PI or delegated staff at each site must record all eligible patients for trial registration who are discussed at the MDT, identified as potentially eligible on the baseline MRI report and/or identified by review of case notes. When patients are discussed but not approached or the patient chooses not to participate in the study please ensure these patients are still entered in the site screening log and the reason for non-inclusion documented. A registration log and randomisation log including reasons for non-inclusion should also be maintained for TRIGGER for patients registered and randomised. The reason and rate of non-recruitment at each step are important end points for the feasibility study.

## 7.2 PATIENT ID NUMBER

Each patient registered will be assigned a unique patient trial number at the time of registration with the TRIGGER Trial Office once eligibility has been confirmed. The trial number is a three-digit number, starting with 001 and increasing in ascending order, and is provided by the TRIGGER Trial Office at the Royal Marsden. This trial number will be a unique identifier and the primary way the patient will be identified during both the registration stage and following randomisation and should be used in all correspondence throughout the registration and subsequent trial periods. This trial number will be used to identify tumour blocks/slides and blood samples sent to the central laboratory. The patient's initials will also be used to cross-reference these samples.

## 7.3 REGISTRATION PROCEDURE

- Prior to registration confirm the patient's potential eligibility by reviewing history, diagnosis and treatment plan discussed at MDT referring to eligibility criteria in Section 6.
- Provide patient with PIS1 and seek patient's consent during the 4 weeks prior to CRT commencing.
- Once consent obtained, complete the Eligibility Checklist in the **TRIAL REGISTRATION Form** which must be signed by the registering investigator.
- Complete the remaining sections of the **TRIAL REGISTRATION Form** and **CONCURRENT MEDICATION Form**.
- Complete the **BASELINE MRI (PRE-CRT) Form**, which must be signed by the Radiologist.
- Ask patients to complete the **QUALITY OF LIFE Form** (EORTC QLQ-C30, LARS, EQ-5D).
- If patient consented to optional blood sample collection, obtain the required blood samples as described in section 10.4 and the Laboratory Manual.
- Submit the following documents by fax to the TRIGGER trial office at the Royal Marsden:
  1. Confirmation of patient consent for registration (Consent Form 1)
  2. TRIAL REGISTRATION Form
  3. CONCURRENT MEDICATION Form
  4. BASELINE MRI (PRE-CRT) Form
  5. QUALITY OF LIFE Form
  6. Histopathology report confirming diagnosis\*
  7. MRI Report\*
  8. A copy of the MDT Notes\*

**\* These documents should be anonymised prior to sending to the Trial Office by removing patient identifiers (including name, date of birth, NHS or hospital number) and adding trial name, site ID number and patient initials only.**

**Send by fax to: [name], Trial Manager, F: [name]**

**Department of Radiology, Royal Marsden Hospital, [name]**

- Once the trial staff from the TRIGGER Trial Office have confirmed eligibility the site will be informed of the patient's allocated unique trial number (see Section 7.2 above). **This trial number should then be added to all trial-related patient documentation associated with registration including documents 1-8 listed above.**
- Contact local pathology department to arrange for the release of the tumour block for transfer to the central laboratory and provide them with a copy of the patient registration consent form.

### **7.3.1 HISTOPATHOLOGY INFORMATION AND CLINICAL INVESTIGATIONS REQUIRED AT REGISTRATION**

- Histopathology - biopsy confirmed adenocarcinoma
  - date of biopsy, name of pathologist, tumour grade:
    - Well-differentiated adenocarcinoma
    - Moderately differentiated adenocarcinoma
    - Poorly differentiated adenocarcinoma
    - Undifferentiated
- Baseline MRI staging
- Results of the most recent routine blood tests performed prior to CRT as per local practice to determine there are no contraindications to planned choice of systemic chemotherapy.
- List of Concomitant medications including medication, dose, frequency and indication
- For female patient the result of most recent pregnancy test result (urine/blood) performed prior to commencing CRT as per local practice.

### **7.4 RANDOMISATION PROCEDURE**

- Provide patient with PIS2 (Randomisation) at a routine outpatient appointment during CRT, ensuring patients are given a minimum of 24 hours between receiving this PIS and obtaining informed consent. It is anticipated that patients will receive PIS2 during the first three weeks of CRT allowing ample opportunity to ask questions and discuss the different treatment plans associated with randomization arm and the two interventional arm sub-groups.

- Once consent obtained complete the **RANDOMISATION Form** which must be signed by the PI (or delegate).
- Send the following documents to the TRIGGER Trial Office at the Royal Marsden, as soon as possible after consent has been obtained:

- Confirmation of patient consent to randomisation (Consent Form 2)
- **RANDOMISATION Form**

**Send by fax to: [name], Trial Manager, F: [name]**

**Department of Radiology, Royal Marsden Hospital, [name]**

- Randomisation will occur once the trial staff have confirmed patient eligibility. Randomisation will be performed by the Clinical Trials & Statistics Unit at the Institute of Cancer Research using the stratified randomisation method described in section 3.2
- **The result of randomisation will be faxed to the site. This should be filed in the patient's source notes.**
- The following CRFs should also be completed and sent to the TRIGGER Trial Office:
  - **CONCURRENT MEDICATIONS Form**
  - **CHEMORADIOTHERAPY Form** (this should be completed once the patient has finished CRT)

#### **7.4.1 ACTING ON THE RANDOMISATION**

The post-treatment MRI forms are different for the control and intervention arms of the trial – named **CONTROL ARM POST-TREATMENT MRI Form** and **INTERVENTION ARM POST-TREATMENT MRI Form** for the control and intervention arm respectively. Therefore it is crucial that the research team at each site inform the radiologist which arm the patient is in. We recommend that this is done by adding the allocated arm of randomisation and which POST-TREATMENT MRI Form to use to the radiology request card. As this is an open label study, the randomisation outcome should also be recorded in the patient's medical records.

The **CONTROL ARM POST-TREATMENT MRI Form** for the control arm does not include the mrTRG classification. Without this information, treatment should be planned according to current guidelines i.e. only the information from the baseline MRI should be used. If the patient is randomised to the intervention arm, mrTRG directed management should take place.

#### **7.4.2 REGISTERED PATIENTS WHO DO NOT CONSENT TO RANDOMISATION**

Patients may register into TRIGGER but then decide not to consent to randomisation. Documenting the reasons for non-consent at this stage is important for assessing trial feasibility and therefore the reason for non-consent to randomization should be recorded on the Registration log.

## 7.5 WITHDRAWAL CRITERIA

By consenting to the trial, patients should understand that they are consenting to follow-up, data collection, additional MRI scans, additional endoscopy (in some patients) and the (optional) collection of biological samples for future research and (mandatory) central review of archived tissue samples.

Patients have the right to withdraw fully or partially from the study at any time and for any reason without prejudice to his or her future medical care. In cases of full withdrawal the **STUDY WITHDRAWAL Form** should be completed, including the primary reason for withdrawal, and details should be recorded in the patient's hospital records.

### Withdrawal of consent to data collection

Withdrawal of **full** consent for the trial means that the patient does not wish to receive any further trial treatment and does not wish to or is unable to continue with further study participation. The Investigator should discuss with the patient the most appropriate way to withdraw to maintain the patient's care. In this case the patient's data already collected up to the point of withdrawal will still be included in the analysis of data unless the patient has explicitly requested that none of the data collected should be used for analysis. Once the **STUDY WITHDRAWAL Form** is completed no further CRFs should be completed and no further data sent to the Royal Marsden except for serious adverse event data, which will continue to be collected for 30 days after the last dose of systemic chemotherapy (IMP) is received, even if the patient has withdrawn from the study.

### Withdrawal of partial consent

Withdrawal of **partial** consent means that the patient does not wish any further trial treatment any longer but is still willing to provide further data by continuing on study i.e. participate in subsequent study visits or procedures.

### Replacement of patients following withdrawal

Patients who are withdrawn from the trial after randomization due to non-compliance with the protocol (section 7.5.1 below) or patients who withdraw full consent will be replaced in this feasibility trial.

#### 7.5.1 NON COMPLIANCE WITH THE PROTOCOL

Patients will be withdrawn from the study if the post-CRT MRI is performed more than 10 weeks following the completion of CRT or a failure to comply with the deferral of surgery follow-up protocol. A **STUDY WITHDRAWAL Form** should be completed.

#### 7.5.2 DISCONTINUATION OF TRIAL TREATMENT

A patient may discontinue trial treatment whenever continued treatment is no longer in the patient's best interests, but the reasons for doing so must be recorded on the **DISCONTINUATION OF TRIAL TREATMENT**

**Form.** The patient will continue to be followed-up unless they withdraw full consent to further data collection. If the patient gives a reason for their decision, this should be recorded. Reasons for discontinuing trial treatment may include:

- 1) The patient chooses to proceed to surgery despite clinical or radiological evidence of a complete response.
- 2) Disease progression whilst on therapy
- 3) Unacceptable toxicity
- 4) Treatment delayed by more than 3 weeks due to toxicity
- 5) Intercurrent illness which prevents further treatment
- 6) Any alterations in the patient's condition which justifies the discontinuation of treatment in the Site investigator's opinion
- 7) If a female patient becomes pregnant or fails to use adequate birth control (for patients of childbearing potential).
- 8) Any other reason that the patient specifies

In the above cases patients can remain within the trial for the purposes of follow-up and data analysis, unless full consent has withdrawn, according to the treatment option to which they have been allocated.

### **7.5.3 LOSSES TO FOLLOW-UP**

If a patient moves from the area, every effort should be made for the patient to be followed up at another participating trial site and for this new centre to take over the responsibility for the patient, or for follow-up via GP. Details of participating trial sites can be obtained from the TRIGGER Trial Office at the Royal Marsden who must be informed of the transfer of care and follow up arrangements. If a patient is lost to follow-up at a site every effort should be made to contact the patient's GP to obtain information on the patient's status and a **STUDY WITHDRAWAL Form** should be completed.

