b if patient has consented to additional blood sample collection for research.

- c The post-CRT MRI should to be performed within 4-6 weeks (maximum of 10 weeks) from completion of CRT.
- d Both early (4-6 weeks) and late surgical complications (at 12 months) will be recorded.
- e Resected specimen will be prepared and evaluated using a standardized method described in Appendix 5.
- f All adverse events will be recorded from the date the Post-CRT MRI scan is performed until 30 days after the last dose of chemotherapy is administered during the Intervention Phase of the trial.
- g Disease status at 5 years (does not require clinic visit): alive without metastatic or recurrent disease, alive with metastatic and/or recurrent disease (date diagnosed), dead (date of death)
- h Patient consent to randomisation can take place at any time during CRT or once CRT is complete but at least 1 week prior to the post-CRT MRI scan

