## **11. CLINICAL FOLLOW-UP**

Once randomised, patients remain evaluable for the intent-to-treat analysis regardless of their subsequent course and treatment. Follow-up data on all patients, including details of other treatments given, is therefore important.

All patients that undergo surgery will be followed up for 5 years. Patients that defer surgery will be followed up for 10 years. In addition, where available, national mortality records and hospitals episodes statistics will be used to ensure long-term follow-up. If a patient fails to attend a clinic or cannot be followed up, the site should contact the patient's GP to assess their condition.

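### Loss to follow-up is recorded on the form that ends data return for full withdrawals, so, read literally, sites would stop sending later outcome data that the protocol relies on

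*Protocol*

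**What the plan says.** Four parts of the protocol bear on a randomised patient who can no longer be reached in clinic.

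- **Section 7.5.3** asks for every effort to contact the GP about the patient's "status and a STUDY WITHDRAWAL Form should be completed".
- **Section 7.5** gives that form its purpose: "In cases of full withdrawal the STUDY WITHDRAWAL Form should be completed, including the primary reason for withdrawal". The subsection on withdrawal of consent to data collection opens with a definition of giving up full consent ("consent for the trial means that the patient does not wish to receive any further trial treatment"). It then gives the effect of filing the form: "Form is completed no further CRFs should be completed and no further data sent to the Royal Marsden except for serious adverse event data". The exception runs to 30 days after the last chemotherapy dose.
- **Section 11** keeps every randomised patient evaluable for intention to treat, sends the site to the GP when a patient cannot be followed, and adds that, where available, "national mortality records and hospitals episodes statistics will be used to ensure long-term follow-up".
- **Sections 10.1 to 10.3, 11.1 and 11.2** plan disease status at 5 years (surgery) or 10 years (deferral) from clinic or GP records. Footnote g of 10.1 reads "Disease status at 5 years (does not require clinic visit".

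**The concern.** A lost patient has withdrawn no consent, yet is recorded on the form whose completion ends data return. A site that follows 7.5.3 and 7.5 to the letter would stop sending what section 11 requires for that patient. Elsewhere, when consent is intact, the protocol continues follow-up: after treatment discontinuation (7.5.2), after refusal of surgery for regrowth (8.2.2) and under palliative care (11 and 11.2). Section 7.5.3 is out of line with this.

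Three kinds of data are exposed:

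- **3-year pCRM/regrowth status.** Under section 17 an unoperated deferral patient counts as pCRM negative only if regrowth-free at 3 years, and the pCRM rate is a secondary endpoint of this trial.
- **Unsalvageable regrowth.** Section 14.2.2 says more than 5% may close the trial or stop progression to phase III. It is captured on the ADVERSE EVENT and SURVEILLANCE Forms (Appendix 1, section 2; 11.2.1 footnote d), which are among the forms no longer completed.
- **Disease-free and overall survival.** Sections 3.1 and 14.2.2 carry these data into the phase III analysis.

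**Working it through.** **1. The passages side by side, for a patient lost with consent intact.**

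| Data item | Needed by | After the form, read literally |
|---|---|---|
| GP status obtained at the time of loss | 7.5.3, 11 | can be sent if it precedes the form |
| Later annual, surveillance and regrowth forms | 10, 11.2.1, 17 | stopped |
| 5- or 10-year status from clinic or GP records | 11.1, 11.2 | stopped if returned by the site |
| Serious adverse events | Appendix 1 | allowed to 30 days after the last chemotherapy |
| National mortality and hospital records | 11 | not stated to come through site forms; may be unaffected |

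Mortality records alone would not establish disease-free status.

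**2. The plan's own phase III figure (section 14.1.1).** Inputs are 3-year disease-free survival of 74% v 82%, HR 0.66, 80% power, two-sided 5%, 2:1 allocation (211 control, 422 intervention), 3 years' accrual and at least 3 years' follow-up. Freedman's formula, (1.960 + 0.842)² × (1 + 2×0.66)² / (2 × (1 − 0.66)²), gives 183 events against the stated 184. With exponential hazards λ = −ln(0.74)/3 and −ln(0.82)/3, expected events are 76.2 + 108.1 = 184.3. The figure reproduces, with no allowance for loss.

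**3. Loss unrelated to outcome (rates assumed; all 633 patients under this wording).** With loss hazard γ = −ln(1 − d)/3 and t = λ + γ, expected events per arm are n × (λ/t) × [1 − (e^(−3t) − e^(−6t))/(3t)].

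| Lost by 3 years, d | Expected events |
|---|---|
| 0% | 184.3 |
| 2% | 181.6 |
| 5% | 177.6 |
| 10% | 171.0 |
| 15% | 164.3 |

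This costs information. It does not create bias.

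**4. Loss related to outcome and uneven by arm (all assumed).** Take 74% at 3 years in both arms for patients who stay, loss times uniform over 0–3 years, and a hazard m times higher after loss. Kaplan-Meier censored at loss still estimates 74%. True 3-year survival among those lost is (0.74 − 0.74^m)/((m − 1) × 0.3011), where 0.3011 = −ln 0.74.

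- m = 2: (0.74 − 0.5476)/0.3011 = 0.639
- m = 3: (0.74 − 0.4052)/0.6022 = 0.556

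With 15% lost in intervention and 5% in control, the difference shifts by (0.15 − 0.05) × (0.74 − 0.639) = 1.0 point, or (0.15 − 0.05) × (0.74 − 0.556) = 1.8 points, towards intervention, against a planned 8. With m = 1, or equal loss in both arms, the shift is zero. If only the 90 feasibility patients were affected (90/633 = 14.2%), it scales roughly to 0.14–0.26 points.

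**5. The 5% regrowth criterion.** With 2:1 allocation, 60 of 90 patients are in the intervention arm. The introduction puts complete or near-complete response at up to 30%. Taking that as the good-responder share (an assumption) gives 60 × 0.30 = 18. One event in 18 is 5.6%. One event exceeds 5% for any denominator up to 19 (1/19 = 5.3%), and two events do so up to 39 (2/39 = 5.1%). One or two unreported events could therefore decide the criterion.

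**The case against.** The case on the other side is substantial, and most of it limits the point.

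- **The bar is written for withdrawal of full consent.** This is correct: it reaches lost patients only through the shared form, and 7.5.3 does not itself say that data collection ends. But completing the form is the stated trigger, and no section exempts lost patients.
- **A reader might infer that all further data are barred.** They are not. Serious adverse events are excepted, although only until 30 days after chemotherapy, and nothing routes national records through site forms.
- **A reader might infer that lost patients are replaced.** Section 7.5 replaces those withdrawn for non-compliance, and it says that "patients who withdraw full consent will be replaced in this feasibility trial". A patient who is simply lost is in neither group.
- **A reader might infer that a patient is closed after a cursory enquiry.** Section 7.5.3 asks for every effort, and for transfer or GP follow-up when a patient moves.
- **A reader might infer that these patients are censored informatively.** That is a risk only. The protocol states no censoring rule and no loss rate.
- **Uneven loss may come from 7.5.1 instead.** A deferral patient who stops attending may be withdrawn there for not complying with the follow-up schedule, so amending 7.5.3 alone would not remove that loss. The heavier schedule also applies only to those who defer, not to the whole intervention arm. This stands.
- **Disease-free survival is not an endpoint of this protocol.** Censoring rules do belong in the phase III protocol or the analysis plan. Neither can restore data that sites were told not to send, and pCRM and regrowth are endpoints here.

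**Conclusion.** The conflict is real, and it is in the wording: the form required by 7.5.3 carries a rule that, taken literally, stops later site-returned data that sections 11, 11.1, 11.2 and 17 need. The consequence is avoidable loss of 3-year pCRM/regrowth status, unsalvageable-regrowth data and the survival data pooled into phase III. The primary endpoint, randomisations per month, is unaffected.

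No size can be read from the protocol. The event losses assume the stated loss rates and that the wording carries through all 633 patients. The 1.0–1.8 point shift further assumes a tenfold-of-one-percent-step contrast of 15% v 5% lost and a two- to threefold hazard after loss, and it is zero if either condition fails. The point merits an amendment because the repair is nearly free and uses sources already planned. It does not show that any analysis is biased.

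**What to change.** - **Section 7.5.3:** replace the STUDY WITHDRAWAL Form with a 'lost to clinic follow-up' entry on the ANNUAL FOLLOW-UP Form, giving the date last known alive and disease status. State that GP, clinic-record, national-record and 5- or 10-year status collection continue unless full consent is withdrawn.
- **Section 7.5:** state that the bar on further data applies only to patients who withdraw consent to data collection.
- **Section 7.5.1:** it uses the same form for non-compliance. Reconcile that use with the limited bar and with the intention-to-treat statement in section 11; otherwise deferral patients who stop attending could still be closed by that route.

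The cost is a few sentences of amendment and one tick-box on an existing form. No visits are added and no new data source is needed.
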